### Statistical methods and analysis

Descriptive statistics will compare cluster-level and patient-level baseline characteristics between the two treatment groups.

Results will be analyzed using a generalized estimation approach for fitting logistic regression using a population-averaged method with treatment arm and stratification variables (i.e. organization type and cluster size) regarded as fixed effects and clinic (i.e. cluster) as random effects in the model. To account for clustering, an exchangeable correlation matrix and robust standard errors will be specified [45]. The intra-cluster correlation coefficient will be estimated, and if it is found to be negative, an analysis not adjusting for clustering will be used.

The following baseline variables will be treated as potential confounders: gender; age; body mass index; identifying as First Nations, Inuit or Métis; household income; employment status; educational attainment; depression; AUDIT-C score; heaviness of smoking index; marijuana use; opioid use; treatment for mental health problem; drug treatment; and comorbid conditions. To identify the covariates to be included in the statistical models for the primary, secondary and tertiary analyses, we will fit separate models including each covariate one at a time. The final model will include those covariates such that their inclusion changes the estimated treatment effect by at least 10%. Decisions about the inclusion of covariates will not be based on statistical significance (i.e. *p* values).

As the primary and secondary outcomes will be captured by the online portal, complete case analyses will be used (i.e. imputation will not be used for these outcomes). The tertiary outcome will be available only for those patients who complete a 6-month follow-up survey; therefore, missing data is expected. A single imputation of best-case scenario (i.e. not smoking and drinking within guidelines) and a single imputation of worst-case scenario (i.e. smoking and drinking in excess of guidelines) will be conducted. If the best-case and worst-case scenarios imply different conclusions, a multiple imputation approach that accounts for the clustered structure of the data will be employed.

All analyses will follow an intention-to-treat approach in which clusters and participants are analyzed in the intervention arm to which they were originally assigned.

Qualitative interviews are taking place with health care practitioners to examine the facilitators and barriers of implementing SBIRT within their practice, as well as the diffusion of knowledge to others within their practice. We will analyze the interviews using a hybrid approach of inductive and deductive coding [46].

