### Blinding

This pragmatic, cluster trial is designed to evaluate an intervention to change practitioners’ behaviour. Blinding of the clinic via its practitioners will therefore not be possible as the practitioner will be aware of the presence or absence of the portal prompting system.

Participating clinics will not be told of their treatment allocation until the trial begins. Investigators are blinded to the randomization arm. Data analysis will be blinded to treatment allocation.

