### Effect size

Based on measures of alcohol consumption used in the STOP Program prior to the start of the COMBAT trial, and accounting for intra-cluster correlation within each clinic as well as unequal enrollment by clinic, we assumed an enrollment of 23 participants per clinic over the 12-month course of this trial, in 189 clinics, for a total of 4347 subjects exceeding CCS guidelines, with enrollment size varying by a coefficient of 1.04. We set alpha = 0.05 and power = 80% and estimated an intra-cluster correlation coefficient of 0.04. Since there were no available estimates of the trial’s primary outcome measure prior to the initiation of the trial, the minimum detectable effect size was estimated for a range of values of *P*
_1_, the proportion of control group enrollments in which practitioners delivered the brief intervention. The estimated detectable effect size ranged from a relative risk of 1.45 (if *P*
_1_ = 0.1) to 1.04 if (*P*
_1_ = 0.9).

An interim analysis in the form of a power calculation was conducted at the 8-month mark once estimates of *P*1 (defined above) were available. As described above, we used a method that accounts for intra-cluster correlation within each clinic as well as unequal enrollment by clinic, now incorporating the updated measures of alcohol consumption introduced with the start of the trial. The observed average cluster size was 12.71 and cluster sizes varied by a coefficient of 1.38. Setting alpha = 0.05, the analyst, unblinded to treatment allocation, obtained an estimate of *P*
_1_ from the data collected to that date. To detect a relative risk of 1.20, the required sample size was estimated to be 6158. Therefore, the recruitment period will be extended until such a time as that sample size is achieved.

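### The covariates of the primary model are picked by a one-at-a-time 10% change-in-estimate rule on an unstated scale; a set fixed in advance would be a cheap improvement.

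*Protocol article*

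**What the plan says.** Under Statistical methods and analysis, the protocol article specifies a population-averaged logistic regression with treatment arm and the two stratification variables (organization type and cluster size) always in the model. It then gives a list that begins "The following baseline variables will be treated as potential confounders: gender; age; body mass index" and runs to 15 items, ending with comorbid conditions.

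The selection step applies to all three tiers of outcome, and candidates are tried singly: "we will fit separate models including each covariate one at a time". Then: "The final model will include those covariates such that their inclusion changes the estimated treatment effect by at least 10" per cent. P values play no part: "Decisions about the inclusion of covariates will not be based on statistical significance".

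The article does not say whether the 10% applies to the odds ratio, the log odds ratio or another measure. It names no primary model other than the one this procedure yields. The Randomization section allocates clinics 1:1 within six strata.

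**The concern.** The rule decides what goes into the primary model by looking at the treatment estimate. Four consequences follow.

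- The adjusted odds ratio that will be reported, and the covariates it is conditional on, are unknown until the outcome data are in. They can differ between the primary, secondary and tertiary outcomes.
- The threshold is a fraction of the estimate. The smaller the estimated log odds ratio, the smaller the shift that counts as 10%, so on that scale selection is most frequent near the null, where the conclusion is most fragile.
- A covariate that predicts the outcome but is well balanced barely moves the estimate, so it tends to be left out, although such covariates can add precision.
- With the scale unstated, two analysts could follow the text faithfully and fit different models.

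At stake is how far the primary estimate is fixed in advance, and in a minority of trials whether it is declared significant.

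**Working it through.** **Inputs from the protocol article.** Effect size section: alpha 0.05, power 80%, ICC 0.04; planning values of 189 clinics, 23 patients per clinic (189 × 23 = 4347), coefficient of variation (CV) 1.04; revised values of CV 1.38, relative risk (RR) 1.20, N = 6158. Participants section: 221 clinics. The interim estimate of P1, the control proportion, is not given.

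**Reproducing the plan's own figure.** The design effect for unequal clusters is DE = [1 + (m − 1)·ICC] / [1 − CV²·L(1 − L)], with L = m / [m + (1 − ICC)/ICC].

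- L = 23/(23 + 24) = 0.489.
- DE = 1.88 / (1 − 1.0816 × 0.2499) = 1.88/0.730 = 2.576.
- Effective n per arm = 4347/2/2.576 = 843.6.
- A two-sided two-proportion test with 80% power then detects RR 1.447 at P1 = 0.1 and 1.041 at P1 = 0.9. These match the stated 1.45 and 1.04, so the planning inputs are sound for what follows.

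**Assumed P1.** Under two unequal-cluster design effects, and cluster sizes from 12.71 to 6158/221 = 27.86, N = 6158 at RR 1.20 implies P1 of about 0.25 to 0.36. P1 = 0.3 is used.

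**What 10% means on each scale (P1 = 0.3, RR 1.20).** P2 = 0.36, OR = (0.36/0.64)/(0.30/0.70) = 1.3125, log OR = 0.272.

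- 10% of the log OR: the OR moves to exp(0.9 × 0.272) = 1.277 or exp(1.1 × 0.272) = 1.349.
- 10% of the OR: the OR moves to 1.181 or 1.444. That is ln(0.9)/0.272 = −39% or ln(1.1)/0.272 = +35% of the log OR.

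At the ends of the plan's own range, 10% of the OR is −24.9%/+22.5% of the log OR (P1 0.1, RR 1.45) and −21.7%/+19.6% (P1 0.9, RR 1.04). The two readings are about two to four times apart.

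**Simulation.** 400 trials per scenario, logistic model with cluster-robust standard errors under working independence, strata omitted. Assumed covariates: 15 standard normal variables with ICC 0.05; five with log OR β per SD, five with β/2, five with zero.

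| N, clinics, CV | P1 | RR | β | at least one enters, log OR | mean number | at least one enters, OR | selected vs unadjusted disagree on significance |
|---|---|---|---|---|---|---|---|
| 4347, 189, 1.04 | 0.5 | 1.00 | 0.30 | 94.8% | 5.26 | 0% | 2.2% |
| 4347, 189, 1.04 | 0.5 | 1.05 | 0.30 | 89.5% | 4.76 | 0% | 4.0% |
| 4347, 189, 1.04 | 0.5 | 1.13 | 0.30 | 61.5% | 1.57 | 0% | 9.8% |
| 6158, 221, 1.38 | 0.3 | 1.00 | 0.30 | 93.0% | 5.22 | 0% | 3.3% |
| 6158, 221, 1.38 | 0.3 | 1.20 | 0.30 | 48.2% | 1.32 | 0% | 4.5% |
| 6158, 221, 1.38 | 0.3 | 1.00 | 0.15 | 72.8% | 3.44 | 0% | 0.5% |
| 6158, 221, 1.38 | 0.3 | 1.10 | 0.15 | 48.2% | 1.99 | 0% | 0.5% |
| 6158, 221, 1.38 | 0.3 | 1.20 | 0.15 | 14.5% | 0.38 | 0% | 0.7% |

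Null rejection rates (three scenarios with RR 1.00): 5.8 to 7.2% unadjusted, 7.0 to 8.0% under the rule on the log-OR scale, 6.0 to 8.5% with all 15 covariates. The simulation error of one rate near 7% is √(0.07 × 0.93/400) = 1.3 points, so these do not differ.

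**Balanced prognostic covariates.** Integrating over one perfectly balanced normal covariate with log OR 0.5 per SD, at RR 1.20 and P1 from 0.1 to 0.7, inclusion moves the log OR by 2.5 to 5.8% and the OR by 0.5 to 3.5%. Neither reaches 10%, so the rule leaves out even a fairly strong predictor if it is balanced.

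**The case against.** The rule is written down in advance, uses named variables and a numeric threshold, and avoids p values. The scale is a detail that an analysis plan commonly settles. On the odds-ratio reading almost nothing enters, and the model falls back to treatment plus strata, which is already fixed. These points stand as limits on the harm. They do not remove the rule, which the article itself states and which makes the final model depend on the estimate.

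Several stronger readings are tempting and are not supported:

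- *All baseline differences are chance, so adjustment is pointless.* Only clinics are randomised. The Blinding and Patient screening sections show that practitioners who know their arm enrol patients afterwards, so systematic imbalance is possible. That supports adjusting for patient covariates. It does not support choosing them by their effect on the treatment estimate.
- *The rule inflates type I error.* A separate simulation of 1,500 trials per scenario gave 7.4% with the rule and 6.5% with a fixed set of five, with a Monte Carlo standard error of 0.7 points. The gap of 0.9 points is within simulation error, and the results above agree.
- *Non-collapsibility of the odds ratio drives selection.* For one balanced covariate the shift is below 10% at the strengths considered.
- *Missing covariates will shift the estimates through changing samples.* The sentence "complete case analyses will be used (i.e. imputation will not be used for these outcomes" concerns the primary and secondary outcomes. The article says nothing specific about missing covariates and may leave that to the analysis plan.
- *An unblinded analyst can steer the model.* The Blinding section says "Data analysis will be blinded to treatment allocation", while the Effect size section reports that "the analyst, unblinded to treatment allocation, obtained an estimate of" P1. That tension is a separate matter: the unblinded step was a power calculation, and the selection rule is mechanical and can be run with masked arm labels.

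**Conclusion.** The point holds in a limited form and is a cheap improvement; it does not invalidate the primary analysis. The rule makes the final model for every outcome depend on the data, and leaves open a choice of scale that decides whether covariates enter often or hardly ever. The effect on the significance conclusion is small to moderate: 0.5 to 10% of simulated trials, against the unadjusted model and on the log-OR reading.

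The selection rates rest on assumed covariate strengths (β of 0.15 or 0.30 per SD), an assumed P1, working independence in place of the planned exchangeable correlation, and omitted strata. The scale arithmetic depends only on P1 and RR. That the model is chosen from the estimate follows from the text alone.

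**What to change.** Define the primary model as treatment, the randomisation strata and a short set named from the listed baseline variables. Choose the set before unblinding, on expected prognostic value or plausible differential enrolment, and use it for the primary, secondary and tertiary outcomes. Keep the 10% rule only as a labelled sensitivity analysis, with its scale stated.

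The cost is wording. The article reports that primary and secondary outcome data are still being collected, so at that stage the change could precede the final analysis. The small downside is that a chance imbalance in a variable outside the named set is dealt with only in the sensitivity analysis.

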### Outcomes

The primary outcome of the study, measured at the cluster level, will be the offer of an appropriate educational alcohol resource, reduction or abstention, to patients exceeding the cancer prevention alcohol consumption guidelines upon completion of STOP smoking cessation program enrollment. This dichotomous outcome is recorded by the STOP program’s online portal for each enrolling participant.

Given that patients can refuse practitioners’ offer of resources, the secondary outcome of the study, measured at the cluster level, will be the acceptance of the educational alcohol resource by patients exceeding the cancer prevention alcohol consumption guidelines. This dichotomous outcome is also recorded by the STOP program’s online portal for each enrolling participant.

The tertiary outcome, measured at the patient level, will be patient abstinence from smoking, and alcohol consumption within cancer prevention guidelines, at the 6-month follow-up survey as recorded in the STOP program’s online portal. Smoking abstinence will be defined by a negative response to the seven-day point prevalence question, “Have you had a cigarette, even a puff, in the last 7 days?” Alcohol consumption at follow-up will be measured using the same survey items as those used in the baseline enrollment survey, described previously. Alcohol consumption within CCS guidelines will be defined as the inverse of alcohol consumption in excess of CCS guidelines.

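### Multiple imputation of the 6-month outcome depends on disagreement between two single imputations that do not bracket the treatment effect, so their agreement does not show robustness

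*Protocol article*

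**What the plan says.** The Outcomes section defines the endpoint: "The tertiary outcome, measured at the patient level, will be patient abstinence from smoking, and alcohol consumption within cancer prevention guidelines", assessed at the 6-month survey. Statistical methods and analysis acknowledges the gap in the data: "The tertiary outcome will be available only for those patients who complete a 6-month follow-up survey; therefore, missing data is expected". It then sets two fill-ins. One is "A single imputation of best-case scenario (i.e. not smoking and drinking within guidelines"); the other is "a single imputation of worst-case scenario (i.e. smoking and drinking in excess of guidelines) will be conducted". Both are defined by the outcome value, and neither mentions treatment arm. The next sentence is the trigger: "If the best-case and worst-case scenarios imply different conclusions, a multiple imputation approach" that respects the clustering is used.

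The analysis model is "a generalized estimation approach for fitting logistic regression using a population-averaged method", so the natural effect measure is an odds ratio. Complete-case analysis is stated for the primary and secondary outcomes only. The article does not define what counts as different conclusions, and does not say which tertiary estimate is reported when the scenarios agree.

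**The concern.** A best-case/worst-case pair is useful when it spans the effects that the missing data could support. This pair does not, because the same value goes to missing patients in both arms. With similar missingness by arm, both scenarios pull the risk difference towards zero by the same factor. Their agreement may then reflect shared dilution, but the rule takes it as sufficient and stops there.

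What remains is two deterministic imputations that differ only in an arbitrary fill-in value and carry no imputation uncertainty. At stake are the size and interval of the trial's only patient-level outcome. The abstract's discussion makes improvement in such outcomes one of the grounds for using the tool as a model elsewhere, and the Discussion concedes that power for this outcome is uncertain.

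**Working it through.** **The plan's own figure.** The Effect size section gives detectable relative risks of 1.45 to 1.04, for the primary outcome only. Inputs: "We set alpha = 0.05 and power = 80"%, "estimated an intra-cluster correlation coefficient of 0.04", 23 patients per clinic, coefficient of variation 1.04, 4347 patients.
- L = 23/(23 + 0.96/0.04) = 0.489.
- Design effect = (1 + 22 × 0.04)/(1 - 1.04² × 0.489 × 0.511) = 1.88/0.730 = 2.58.
- Effective n per arm = 2173.5/2.576 ≈ 844, which gives relative risks of 1.447 and 1.041. The stated range is reproduced.

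There is no corresponding figure for the tertiary outcome or its missingness.

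**Algebra.** Let responder success be p0 and p1, with fractions d0 and d1 missing.
- Worst case: RD = (1 - d1)p1 - (1 - d0)p0.
- Best case: RD = worst-case RD + (d1 - d0).
- If d0 = d1 = d, both equal (1 - d)(p1 - p0).

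**Assumptions (not in the article).** Success is 25% v 30% in responders. There are 3079 patients per arm (6158/2, the revised sample size) and a design effect of 2, so effective n ≈ 1540 per arm. Missingness is equal by arm and unrelated to outcome. Conclusions are read as two-sided 5% significance with direction. The observed-data test stands in for multiple imputation under missing at random. Effects below are at the assumed rates; percentages come from 200,000 simulated trials per row.

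| Missing | RD, both scenarios | OR observed / worst / best | Scenarios agree | Both null, observed data significant |
|---|---|---|---|---|
| 30% | 3.5 points | 1.29 / 1.25 / 1.15 | 64% | 1.8% |
| 50% | 2.5 points | 1.29 / 1.24 / 1.11 | 57% | 3.8% |
| 60% | 2.0 points | 1.29 / 1.23 / 1.10 | 59% | 4.8% |

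Example of the odds ratios at 60% missing:
- Worst-case rates are 0.10 and 0.12: (0.12/0.88)/(0.10/0.90) = 1.23.
- Best-case rates are 0.70 and 0.72: (0.72/0.28)/(0.70/0.30) = 1.10.
- Responders: (0.30/0.70)/(0.25/0.75) = 1.29.

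**Intervals at 60% missing.** The variance of the log odds ratio is the sum over arms of 1/[n p(1 - p)], with n = 1539.5 for the imputed data and 615.8 for responders.
- Observed: SE 0.128, 95% CI 1.00 to 1.65.
- Worst case: SE 0.116, 95% CI 0.98 to 1.54.
- Best case: SE 0.079, 95% CI 0.94 to 1.29.

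The risk-difference z values are 1.97 (observed), 1.77 (worst) and 1.22 (best). Both scenarios are null here, so multiple imputation would not run, although the two intervals differ materially.

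**Sensitivity.** With 20% v 25%, 50% missing and design effect 2.437 (from the 8-month cluster size of 12.71 and coefficient 1.38: 1 + [(1 + 1.38²) × 12.71 - 1] × 0.04), agreement is about 57%. Both scenarios are null with significant observed data in about 4% of trials. The picture does not depend on one choice of rates.

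**What would bracket the effect.** At 20% v 25% with 50% missing, arm-opposed fill-ins give 0.125 + 0.5 - 0.10 = +0.525 and 0.125 - (0.10 + 0.5) = -0.475. The planned pair gives +0.025 twice.

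**The case against.** Several points on the other side stand.

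- **Effect scale.** The plan fits a logistic model. Worst-case dilution of the odds ratio is slight, and the worst-case relative risk under equal missingness is unchanged (0.12/0.10 = 1.20 = 0.30/0.25). Large dilution on these scales is confined to the best case.
- **Conclusions.** A reader might infer that the rule often turns a real effect into a reported null. The simulations do not support that: it happens in about 2-5% of trials at 30-60% missing, and about 1% at 20%. The 60% example, with observed z of 1.97, is a borderline case.
- **Differential missingness.** A reader might also infer that the rule fails when one arm loses more patients. Large differences usually set off the trigger, because the two risk differences are d1 - d0 apart. With no true effect (25% in both arms) and 45% v 55% missing, the scenarios agree in only 0.2% of trials, so multiple imputation almost always runs.
- **What is reported.** The article does not say that a single imputation is the reported estimate when the scenarios agree, and a fuller document may name one. It would go too far to say that the reported effect will be diluted. What can be said is that no other tertiary estimate is stated.
- **Missing at random.** Dilution is measured against the responder contrast. If every non-responder had in fact failed, the worst case would be right. Multiple imputation rests on its own untestable assumption and does not remove the need for sensitivity analyses.

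These points limit the size of the problem. They do not rescue the trigger: agreement between two scenarios that shrink the same contrast is not a check on the missing-data assumption.

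**Conclusion.** The concern holds, at minor to moderate severity. The stated rule withholds cluster-aware multiple imputation on the strength of an agreement that carries little information about robustness. Under the assumed rates this happens in about 57-64% of trials with equal missingness. It leaves an estimate and interval that depend on the fill-in value: a 5.0-point difference becomes 2.0-3.5 points, and an odds ratio of 1.29 becomes 1.23-1.25 or 1.10-1.15. The damage is mainly to the estimate and its precision and seldom to the significance verdict.

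The success rates, missingness and design effect are assumptions, as the article gives none for this outcome. The algebraic result, equal shrinkage of the risk difference under equal missingness, needs none of them beyond imputation by value regardless of arm, which is the plain reading of the text.

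**What to change.** Delete the trigger. Make the cluster-aware multiple imputation that the plan already foresees the tertiary analysis in all cases, using the baseline covariates already collected (for example AUDIT-C score, heaviness of smoking index, age and gender).

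Keep missing = smoking and exceeding guidelines as a sensitivity analysis. Because multiple imputation assumes missing at random, add a delta-adjusted tipping-point analysis with arm-specific shifts. Full arm-opposed extremes would bracket the effect but, at the missingness assumed here, are too wide to inform.

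The cost is a change of wording and a little more programming; no new data are needed. The change should be fixed before the tertiary data are analysed by arm. At submission, the trial-status section listed only baseline, primary and secondary data collection as in progress.
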